**Patient Satisfaction outcomes**

Patients’ satisfaction towards the clinical encounter outcomes with their therapist will be assessed through a survey distributed upon discharge or after the 6-weeks data collection period of the study (T3). The Visit-Specific Satisfaction instrument (VSQ-9) [21] consists of a 9-item self-report questionnaire, which aims to rate the overall satisfaction of the patient toward his clinical encounter with a healthcare professional. The patient has to rate each item on a scale from “poor” to “excellent”. The score is then transformed linearly to a 0 to 100 scale, with 100 corresponding to “excellent” and 0 to “poor”. Then, a VSQ-9 score for each person is created based on the average response score on all of the 9 items. An adapted version will be used according to the context of the study (see [Appendix D](#_Annex_D)).

**Preliminary effect outcomes**

The secondary outcomes measures will assess the preliminary effects of the intervention. We will first obtain sociodemographic characteristics (i.e. age, sex, educational level, clinical setting, completed continued education in the last 5 years) of the participating PTs at the training seminar using self-administered questionnaires. We are also going to determine the percentage of patients that fall into the different subcategories of the model. This will allow us to explore all possible subgroups of patients based on the PDDM.

The documentation of the preliminary short-term (T2: initial visit; T3: final visit, +6 weeks) clinical effects of the use of the model will be assessed through the analysis of the core outcome measures for the five domains of the PDDM (see Table 1). Dyads (PTs and patients) will have to complete the questionnaires below and enter all the relevant data in the electronic survey (Excel). The number of visits will also be reported during the treatment period. The participating PTs’ patients will have to complete baseline assessments (T0) and final assessment (T1) based on the outcome measures identified related to the five domains of the PDDM model and a sociodemographic and health questionnaire (age, sex, comorbidities, medication) already used in both clinical settings. Following their training, the PTs will have the adequate knowledge to perform the assessment and support the patients in completing the questionnaires.

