**Methods**

**Design**

A prospective single arm design will be carried out to test the clinicians’ acceptability and the feasibility of the intervention for people with non-specific LBP as well as to gather preliminary data on its effectiveness through quantitative and qualitative methods. The CONSORT statement extension for feasibility trials [15] and the SPIRIT statement list [16] guided the development of this feasibility study protocol.

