**Recruitment**

A convenience sampling method will be used to recruit the clinicians. PTs from the two sites that express interest in participating in the study will be enrolled if they meet the inclusion criteria. An email containing all the relevant and necessary details to participate in the study including the participant’s (PTs) implication and the research team coordinates will be sent to all the clinicians from both sites (see [Appendix A](#_Annex_A:_invitation)). Patients participating in the study will be recruited based on the participating clinicians’ caseload. Each PT will have to recruit participants (new patients) by explaining in detail the purposes, process and implications of participating in the study. A formal consent form with all the aforementioned details will be provided by the PT to the patient. As this is a feasibility trial, no formal sample size calculation was conducted [17]. Instead, we aim to recruit between 10-15 PTs in order to effectively measure the feasibility of implementation of the intervention in a 3-4 months timeframe. We aim to have each PT provide complete data for at least five of their patients with non-specific LBP for an expected total of 50-75 patients.

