Following the training, we estimate that adequate knowledge and skills will have been provided to the participating PTs, enabling them to deliver the intervention to their patients based on the principles of the PDDM model. For each of their patients, the PT will have to provide clinical data based on their use of the PDDM model to guide their assessment and interventions over a 6-weeks period (or less if the patient is discharged before the end of the 6-week period). The data collected relates to the selected outcomes to measure feasibility, acceptability and preliminary effect of the intervention. Concerning the specific use of the PDDM model in order to guide the clinicians’ assessment and treatment approach, an electronic tool using Excel will be developed by the research team. This tool aims to foster the identification by the clinicians of the relative contribution of each domain to the patient health condition by creating a complete personalized profile and to gather baseline patients’ sociodemographic characteristics. This tool will be presented to the PTs during the training seminar.

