**Ethical considerations**

Informed consent from all participants to participate in this study will be obtained. For the PTs, their consent will be obtained via a consent form handed to them at the beginning of the training workshop. Since the patients are already seeking and/or receiving healthcare services, only their consent to fill out questionnaire for the purpose of the study will be obtained by the PTs themselves via a second consent form with detailed information concerning the study process and their implication. In fact, the care received by the patients in this study is in the same continuum of standard care. They will be advised that all collected data would be kept confidential and anonymized by the use of alphanumeric coding only known to the researchers. Patients will receive a 20 $ Amazon electronic gift card to compensate for the time necessary to complete all the questionnaires at the time of the final visit (T3).

All electronic identifiable information will be held on a secure, password-protected database, accessible only to the members of the research team. Paper forms with identifiable information will be held in secure, locked filing cabinets within a restricted area. All paper and electronic data will be retained for at least 5 years after completion of the trial. There is no additional risk or inconvenient for the PT or the patient related to their participation in the study.

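### The treating PT helps patients complete the self-report scales, so influence that differs between T2 and T3 can bias the change scores; the VSQ-9 collection route is not stated

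*Protocol*

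**What the plan says.** Protocol, Preliminary effect outcomes, assigns collection of the Table 1 questionnaires to PT and patient together: "Dyads (PTs and patients) will have to complete the questionnaires below and enter all the relevant data in the electronic survey (Excel". It adds that, once trained, "the PTs will have the adequate knowledge to perform the assessment and support the patients in completing the questionnaires". The Intervention section makes the PT the supplier of data for each patient: "the PT will have to provide clinical data based on their use of the PDDM model to guide their assessment and interventions".

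The same PT has the other contacts with the patient. Under Recruitment: "Each PT will have to recruit participants (new patients) by explaining in detail the purposes, process and implications of participating in the study". Under Ethical considerations, "only their consent to fill out questionnaire for the purpose of the study will be obtained by the PTs themselves". There is no comparator; the Design section states: "A prospective single arm design will be carried out to test the clinicians’ acceptability and the feasibility of the intervention".

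Data analysis defines the effect measure as the T2-to-T3 change on each self-reported questionnaire. (One sentence under Preliminary effect outcomes labels the patient assessments T0 and T1. T2 and T3 are used here, as in Table 1 and Data analysis.)

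The VSQ-9 is described separately, under Patient Satisfaction outcomes. It is given once, at discharge or after six weeks, and is meant to "rate the overall satisfaction of the patient toward his clinical encounter with a healthcare professional". The section does not say who hands it out, collects it or enters it.

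**The concern.** The five questionnaires in Table 1 are meant to record the patient's own view. Here the person helping with the answers has volunteered for the study, was trained by the team that proposed the model, and delivers the care that the answers will be used to judge. Patients may answer more favourably in front of their therapist, and a therapist's explanation of an unclear item can steer the reply. The Protocol describes no private completion, independent assessor or direct return to the research team for these scales.

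The two visits also differ in kind. At T2 the patient is new and the answers feed the PDDM profile. At T3 the patient has had up to six weeks with that PT and the answers reflect the result. There is therefore good reason to doubt that PT influence is the same at both.

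The study is meant to inform a randomised trial. Change scores that are partly a reporting effect would make the model look more promising than it is, and the later trial could inherit the same collection procedure. For the VSQ-9 the risk is that a component of the primary outcomes is collected by the person being rated, because nothing in the text prevents it.

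**Working it through.** **1. The plan's own figure.** Recruitment gives 10–15 PTs with at least five patients each: 10 × 5 = 50 and 15 × 5 = 75, which matches the stated 50–75 patients. No alpha, power, effect size or SD is given, so there is nothing else to reproduce.

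**2. What reaches the change score.** Let b2 and b3 be the mean reporting shifts caused by PT involvement at T2 and T3. Then

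observed mean change = true mean change + (b3 − b2).

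- If b3 = b2, the shift cancels and the change is unbiased.
- If b3 differs from b2, the difference stays in the result. A control arm would remove it only if the difference were the same in both arms; here there is none.

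**3. Direction.** Table 1 labels a PainDetect score of 19 to 38 as positive, so higher is worse. The other four scales, as Table 1 describes them, measure pain and interference, symptoms, or risk of a poor course. A favourable shift at T3 therefore means lower T3 scores.

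**4. VSQ-9.** It is measured only at T3, so observed mean = true mean + b3. No baseline is subtracted. Whether b3 includes any PT effect depends on a collection route that the Protocol does not state.

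**5. Scale, under assumptions.** The documents give no value for b2, b3 or the within-PT correlation (ICC). Working in SDs of the change score, with five patients per PT:

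95% half-width = 1.96 × √[(1 + 4 × ICC) / n]

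| ICC (assumed) | n = 50 | n = 75 |
|---|---|---|
| 0 | 0.277 | 0.226 |
| 0.05 | 0.304 | 0.248 |
| 0.10 | 0.328 | 0.268 |

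With zero true change and ICC 0, the chance that a net shift of b SD produces a 95% interval lying wholly on the improvement side is 1 − Φ(1.96 − b√n):

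| Assumed net shift (SD) | n = 50 | n = 75 |
|---|---|---|
| 0.1 | 0.105 | 0.137 |
| 0.2 | 0.293 | 0.410 |
| 0.3 | 0.564 | 0.738 |
| 0.5 | 0.942 | 0.991 |

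For example, at n = 50 and b = 0.2: 0.2 × √50 = 1.414, 1.96 − 1.414 = 0.546, and 1 − Φ(0.546) = 0.293. A positive ICC widens the interval and lowers these probabilities. The tables show that a net shift of 0.2 to 0.3 SD would be about as large as the sampling error. They do not show that such a shift will occur.

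**The case against.** The strongest reply is that PT support is described for both visits, so its effect may cancel in the change score. That is right for the common part of the influence. It does not cover the part that differs, and the two visits are different enough that equality cannot be taken for granted.

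A second reply is that the effect outcomes are secondary and exploratory, with only change scores planned and effectiveness left to a future trial. This stands. It limits the consequence but does not remove it, because preliminary evidence of change is one of the stated objectives.

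A third is that PT-supported completion is part of what is being tested for feasibility. This also stands, as a cost to weigh.

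Several stronger readings are tempting but not supported:

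- A reader might infer that the outcomes *are* biased. The text supports a risk only, and for the Table 1 scales the likely direction is toward lower scores.
- A reader might infer that the VSQ-9 passes through the PT. The sentence on dyads refers to the Table 1 questionnaires, and the VSQ-9 is not among them. Its route is unstated. Payment for questionnaires completed at the final visit hints at completion in the clinic, but does not say who handles the form.
- A reader might put a figure on the VSQ-9. With five answer levels, one level is 25 points, and if 20–40% of patients answered one level higher on every item the mean would rise by 0.20 × 25 = 5 to 0.40 × 25 = 10 points. The number of levels and the percentage are both guesses, so this is not evidence of size.
- A reader might infer that the PT alone enters and holds the data. Entry is assigned to PT and patient jointly, and the Protocol does not say who keeps the file or whether edits can be traced.

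The alphanumeric coding under Ethical considerations protects collected data. It does not stop the PT from seeing or shaping answers as they are given.

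**Conclusion.** The concern holds as a specific risk of bias. The treating PT is built into completion and entry of the five self-report scales, no safeguard is described, and there is no control arm. Any PT influence that differs between T2 and T3 goes into the change scores, most plausibly toward apparent improvement. Its size cannot be derived from the documents; the figures above rest on assumed shifts, zero true change and, for the probabilities, independent patients. The affected change scores are secondary and exploratory.

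For the VSQ-9 the finding is narrower. A component of the primary outcomes, taken once and rating the encounter with the therapist, has no stated collection route. PT involvement is therefore not excluded, and there is no baseline against which it could cancel.

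**What to change.** - Have patients complete the Table 1 questionnaires by themselves, in the same mode at T2 and T3 (for example an online form or a sealed paper form), without PT help on the answers, and return them to the research team. Changing T3 alone would build a difference in mode into every change score.
- Share the T2 answers with the PT for PDDM profiling.
- State that the VSQ-9 goes directly from patient to research team.
- Tell patients that their PT will not see the T3 answers or the VSQ-9.
- Have the research team import or enter the T3 data.

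The PT can still carry out the clinical assessment and take the comorbidity history.

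The cost is an online or sealed form in place of joint entry in Excel, a quick return of T2 answers to the PT, and a possible small drop in completion without PT help. That drop should be reported with the feasibility results. One asymmetry remains: patients will know that the PT sees the T2 answers but not those at T3. This follows from using T2 for profiling and should be named as a limitation.

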**Table 1. Outcome measures of the five domains of the PDDM model**

| **Domain** | **Specific items** | **Outcome measures (T2 and T3)** |
| --- | --- | --- |
| Nociceptive pain drivers | Pain and impact of pain on physical function | ***Brief Pain Inventory*** (BPI) is designed to assess pain intensity (at its worst, least and average) and the extent to which pain interferes in the daily life in relation to 7 domains of functioning (general activity, mood, walking ability, normal work, relations, sleep and enjoyment of life) on a scale of 0 to 10 [22] (see [Appendix E](#_Annex_E_:)). |
| Nervous system dysfunction drivers | Radicular signs/symptoms, hyperalgesia/allodynia, central sensitization | The ***PainDetect Questionnaire*** [23] is a reliable screening tool to predict the likelihood of a neuropathic pain component. The total score indicates if the pain is less likely to be neuropathic (negative, 0 to 12), uncertain (13 to 18) or like to be neuropathic (positive, 19 to 38) (see [Appendix F](#_Annex_F_:)).  The ***Central sensitization Index*** (CSI) consist of a self-reported tool to assess symptoms of central sensitization (CS) [24, 25]. It contains two sections, part A and B. Part A contains 25 items with 5-point Likert scale with a range for the total score from 0 to 100 and is intended to give an overview of the symptoms that are common in CS. Part B identifies if the patient has been diagnosed with specific disorders associated with CS as well as anxiety and depression (See [Appendix G](#_Appendix_G:_link)). |
| Cognitive-emotional drivers | False-beliefs, fear of pain/movement, illness perception, self-efficacy, mood, | The ***StartBackTool*** (SBT) is a screen­ing questionnaire consisting of 9 items based on psychosocial factors used to categorize patients with LBP based on risk (low, medium, or high) for poor disability outcomes [26]. Overall scores (ranging from 0 to 9) are determined by summing all responses, and the SBT psychosocial subscale (items 5-9; ranging from 0 to 5) are determined by summing all items related to psychosocial factors of prolonged disability such as catastrophizing and pain-related fear and anxiety [26] (see [Appendix H](#_Appendix_H:_link)). |
| Contextual drivers | Job flexibility, occupational factors | The ***Örebro Musculoskeletal Pain Screening Questionnaire*** (OMPSQ) is a 25-items questionnaire used to determine the risk of long-term absenteeism from work due to LBP *based on occupational and social factors* [27]. It also has a shorter 10-items version with comparable predictive properties to those of the long version while being easier to use in clinical settings [28] (see [Appendix I](#_Appendix_I:_link)) |
| Comorbidity drivers | Co-occurring MSK/mental health conditions, | From patient’s history [29] (At T2 only) |

**Timeline**

The timeline of thedata collection process is shown in figure 1 (See figure 1)

**Figure 1. Timeline of the feasibility study**

**
[figure not shown]
**

**Data analysis**

Baseline characteristics will be summarized for all participants (PTs and patients) using descriptive statistics. We are also going to use descriptive statistics to determine the percentage of patients that fall into the different subcategories of the model. Feasibility and acceptability outcomes will be assessed with quantitative descriptive statistics and qualitative reporting of data. Thematic analyses will be conducted on the verbatim transcripts of the semi-structured interviews in order to identify the predominant themes related to the PT’s acceptability of the training workshop and of the assessment procedures. As for the preliminary effect of the intervention on patient outcomes, we will calculate the change (delta score from T2 to T3) for each self-reported questionnaire.

**Ethical considerations**

Informed consent from all participants to participate in this study will be obtained. For the PTs, their consent will be obtained via a consent form handed to them at the beginning of the training workshop. Since the patients are already seeking and/or receiving healthcare services, only their consent to fill out questionnaire for the purpose of the study will be obtained by the PTs themselves via a second consent form with detailed information concerning the study process and their implication. In fact, the care received by the patients in this study is in the same continuum of standard care. They will be advised that all collected data would be kept confidential and anonymized by the use of alphanumeric coding only known to the researchers. Patients will receive a 20 $ Amazon electronic gift card to compensate for the time necessary to complete all the questionnaires at the time of the final visit (T3).

All electronic identifiable information will be held on a secure, password-protected database, accessible only to the members of the research team. Paper forms with identifiable information will be held in secure, locked filing cabinets within a restricted area. All paper and electronic data will be retained for at least 5 years after completion of the trial. There is no additional risk or inconvenient for the PT or the patient related to their participation in the study.

# Appendix B : link to full content of training

[**https://www.dropbox.com/s/sz9jd1n7ejtg3v3/Annexe%20B_Formation_%C3%80%20LA%20RESCOUSSE%20DES%20PERSONNES%20SOUFFRANT%20DE%20LOMBALGIES%20COMPLEXES.pptx?dl=0**](https://www.dropbox.com/s/sz9jd1n7ejtg3v3/Annexe%20B_Formation_%C3%80%20LA%20RESCOUSSE%20DES%20PERSONNES%20SOUFFRANT%20DE%20LOMBALGIES%20COMPLEXES.pptx?dl=0)

# Appendix C – Questions for clinicians (training appreciation)

Appréciation de la formation de la part des cliniciens (guide d’entrevue téléphonique dans la semaine suivant la formation, T1) :

1. Est-ce que le fonctionnement du modèle, de façon générale, fait du sens à vos yeux ? Veuillez me détailler votre réponse.
2. Que pensez-vous de la quantité d’information contenue dans la formation ?
3. Que pensez-vous de la durée de la formation ?
4. Que pensez-vous du déroulement de la formation ?
5. Selon vous, quels sont les points forts/bons coups (ce qui vous a le plus aider) de la formation ?
6. Selon vous, quels seraient les aspects précis de la formation à améliorer ?
7. De manière générale, avez-vous des suggestions afin d’améliorer le déroulement général de la formation ?

Appréciation des ressources disponibles pour supporter l’utilisation du modèle dans la pratique des cliniciens (entrevue téléphonique, T3):

1. Est-ce que les ressources mises à votre disposition pour faciliter l’application du modèle dans votre pratique étaient suffisantes ?
2. Comment avez-vous trouvé l’utilisation des différentes ressources disponibles en termes de facilité d’utilisation, de pertinence et de disponibilité ?
3. Pensez-vous continuer à utiliser ces ressources et le modèle malgré la fin du projet de recherche (intégration à votre pratique?)

# Appendix D : link to Visit-Specific Satisfaction instrument

[**https://www.dropbox.com/s/ul7jyhpv4c6k6g0/Annexe%20D_satisfaction_patients_vsq9_adapted.pdf?dl=0**](https://www.dropbox.com/s/ul7jyhpv4c6k6g0/Annexe%20D_satisfaction_patients_vsq9_adapted.pdf?dl=0)

# Appendix E : link to Brief Pain Inventory

[**https://www.dropbox.com/s/nccv5egw3f6qkpm/Annexe%20E_Bref_Inventaire_Douleur_FR.pdf?dl=0**](https://www.dropbox.com/s/nccv5egw3f6qkpm/Annexe%20E_Bref_Inventaire_Douleur_FR.pdf?dl=0)

# Appendix F : link to Pain Detect Questionnaire

[**https://www.dropbox.com/s/spi48fexcwz0vd2/Annexe%20F_PainDetect_questionnaire_FR.pdf?dl=0**](https://www.dropbox.com/s/spi48fexcwz0vd2/Annexe%20F_PainDetect_questionnaire_FR.pdf?dl=0)

# Appendix G: link to Central sensitization inventory

[**https://www.dropbox.com/s/bxkg1uegkqlb2dc/Annexe G_CSI_fr.pdf?dl=0**](https://www.dropbox.com/s/bxkg1uegkqlb2dc/Annexe%20G_CSI_fr.pdf?dl=0)

# Appendix H: link to StartBack Questionnaire

[**https://www.dropbox.com/s/8906wj6wkugamzg/Annexe%20G_StartBack_FR.pdf?dl=0**](https://www.dropbox.com/s/8906wj6wkugamzg/Annexe%20G_StartBack_FR.pdf?dl=0)

